### Statistical power and sample size

2.6

Sample size estimations were based on meta-analytic evidence for the effectiveness of psychological interventions for BN (Beintner et al., 2014; Haderlein, 2022; Svaldi et al., 2019). Due to the high heterogeneity of effect sizes ranging from medium to large (Beintner et al., 2014; Haderlein, 2022; Svaldi et al., 2019), the sample size needed to detect at least an effect of medium magnitude was estimated using the R package *powerlmm* (Magnusson, 2018). A power analysis with an effect size of *d* = 0.50, an intraclass-correlation of .40 (Arend and Schäfer, 2019), a power of .80, and an alpha-level of .05 resulted in a required sample of *N* = 152. Further power analyses, including possible dropouts, different effect sizes, and intra-class correlations, can be found in the supplementary materials (Figure S2), strengthening our conclusion that our sample size will be sufficiently large to detect a medium effect under different assumptions.

## Discussion

3

Despite the effectiveness of psychotherapy for BN, only a limited number of patients with BN in routine care receive adequate evidence-based treatments (Kessler et al., 2013; Mack et al., 2014). This treatment gap, combined with the high illness-related burden and societal costs of BN, stresses the need to implement alternative treatments for BN (Bode et al., 2017; Kazdin et al., 2017). Applying web-based interventions in routine care might reduce barriers to traditional face-to-face therapies while providing more immediate low-threshold care for patients with BN (Aardoom et al., 2013; Aardoom et al., 2016; Beintner et al., 2014; Dölemeyer et al., 2013; Haderlein, 2022). However, more research on the effectiveness of web-based interventions for eating disorders is needed to evaluate their benefits for the health care system (Beintner et al., 2014; Haderlein, 2022; Linardon et al., 2020; Pittock et al., 2018; Taylor et al., 2021).

Our study aims to address this research gap by examining the effects of using a web-based self-help program for BN in routine care settings. Considering previous promising results concerning the effectiveness of such interventions for BN (Beintner et al., 2014; Haderlein, 2022; Pittock et al., 2018; Taylor et al., 2021), we aim to add knowledge to whether web-based interventions can reduce eating disorder symptoms and improve quality of life in routine care. Moreover, our goal is to explore changes in eating-disorder-related topics such as self-esteem and emotion regulation to better understand possible mechanisms of change.

### Strengths and challenges

3.1

Based on our goal to evaluate the effectiveness of a web-based intervention, our study was designed as a randomized controlled trial with a waitlist control group maximizing the internal validity of results. To further decrease systematic biases, our randomization will follow the principles of sequence allocation concealment, and systematic pre-treatment differences will be minimized by excluding individuals receiving psychotherapy or pharmacotherapy for BN at baseline (Altman et al., 2001; Gupta, 2011). Further, implementing the web-based intervention into a routine care setting will increase the study's external validity. As such, we enhance the generalizability of our results by allowing participants in our trial to receive care as usual after randomization in both groups. Additionally, participants meeting the criteria for other mental disorders will not be excluded as long as their psychological condition allows them to securely participate in a web-based intervention.

Moreover, we aim at contributing to the research on treatments for BN by investigating changes in both cognitive and behavioral eating disorder symptoms. Network analyses indicate that it is possible to differentiate between various types of BN symptoms (Forrest et al., 2018; Levinson et al., 2017), including the number of binge eating episodes, compensatory behaviors, and global eating pathology. Therefore, we will examine changes in these facets separately to better understand whether and how web-based interventions influence different types of BN symptoms. Weekly assessments and naturalistic EMA data will further increase the ecological validity of results and provide more detailed insights into trajectories of change while reducing retrospective biases (Munsch et al., 2007; Munsch et al., 2019).

Apart from investigating changes in eating disorder symptoms, we will analyze whether and how the web-based intervention can help improve participants' daily life. Eating disorders are associated with a broad range of adverse outcomes, and thus examining changes in psychosocial functioning, well-being, and work capacity will help evaluate the web-based intervention from a broader perspective (Colmsee et al., 2021; De Jong et al., 2013; Levinson et al., 2017; Svaldi et al., 2012). Finally, our study will be one of the first to investigate possible mechanisms of change, such as alterations in self-esteem and emotion regulation, which might help advance BN treatment in the future.

Nevertheless, these strengths will probably be associated with some limitations. First of all, to conduct our analyses with adequate power, a high number of participants needs to be included in our study. The recruitment of such a large-scaled sample might be challenging because the prevalence of BN is relatively low, and barriers in the help-seeking process might limit the number of eligible and interested patients (Ali et al., 2016; Becker et al., 2010; Grange and Loeb, 2007; Kessler et al., 2013; Mond, 2014; Puhl and Suh, 2015). To maximize the number of participants and reach the intended sample size, we will employ various recruitment methods, including online and offline advertisement and allowing location-independent participation.

Additionally, the current study does not employ follow-up assessments to investigate the long-term effectiveness of the web-based BN intervention. In general, BN is associated with a high risk for relapses, stressing the need for data on long-term symptom courses following treatment (Quadflieg and Fichter, 2019; Stice et al., 2009). However, follow-up assessments increase the burden for participants and result in longer waiting periods for the control group. Since the web-based program for BN was developed as an add-on to routine care and not as a replacement for face-to-face therapy, the current trial primarily investigates whether adding it into standard clinical practice can immediately improve patients' mental health and quality of life. Moreover, there is no empirical evidence for the effectiveness of the present BN intervention, so focusing on the short-term benefits seems reasonable before testing long-term effects. Still, future studies, including follow-up assessments, should be conducted if the effectiveness of the web-based program can be confirmed.

Another challenge that might occur is a high dropout from the study, which has been frequently reported in previous trials on interventions for eating disorders (Linardon et al., 2018). Low adherence might be especially problematic for the present study, as the high number of assessments combining traditional questionnaires with EMA will lead to a relatively high burden for participants. However, the financial reimbursement and a reminder system, including text messages, emails, and phone calls, will be implemented to encourage participants and hopefully increase adherence (Treweek et al., 2013). Further, we limited the EMA period to five days and included rather short assessment scales respectively only included subscales when possible. Concerning the data analysis, we will follow the intention-to-treat approach and conduct sensitivity analyses to be able to evaluate the influence of possible dropouts (Gupta, 2011). In sum, we are optimistic about being able to assess a high number of outcomes to be able to address our research goals and increase the external validity of results by adding EMA, while keeping dropout rates low.

### Conclusion

3.2

In sum, the contributions of the current study to the growing field of web-based interventions for BN are threefold. First of all, our trial is designed to evaluate whether applying web-based self-help interventions in routine care of BN can help reduce eating disorder symptoms, improve the overall quality of life, and illness-related topics such as psychosocial functioning. Secondly, our study will add knowledge on potential predictors of treatment outcomes and mechanisms of change. This will help us better understand how web-based self-interventions may reduce the burden for patients with BN. Third, by including a broad range of assessment methods and different outcomes instead of focusing only on changes in eating disorder symptoms, we will be able to further investigate whether and how web-based interventions impact the daily life of participants. Based on these innovations, the long-term goal of our research on web-based interventions is to implement evidence-based treatments into routine care, reduce social costs, and enhance the quality of life for individuals with eating disorders.

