Our second goal is to explore how web-based interventions can affect symptom changes and whether patient characteristics influence treatment outcomes. So far, knowledge on moderators, mediators, and predictors of treatment success for internet-based CBT is still limited (Linardon et al., 2017a; Taylor et al., 2021). Thus, we aim at gaining a better understanding of how and why web-based interventions can reduce eating disorder symptoms by investigating possible mechanisms of change. Theoretical models, such as the transdiagnostic theory of eating disorders, and empirical findings stress the importance of psychopathological processes in the development and maintenance of eating disorders (Fairburn et al., 2003; Linardon et al., 2019; MacDonald and Trottier, 2019; Svaldi et al., 2019). Therefore, we will test self-esteem, emotion regulation, and comorbid psychopathology as possible mechanisms of change to address this research gap and help to improve internet-based interventions in the future.

Finally, our trial will incorporate weekly symptom measurements and ecological momentary assessment (EMA) to increase the validity of results and obtain a more nuanced understanding of treatment effects (Munsch et al., 2009; Pruessner et al., 2022; Shiffman et al., 2008).

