#### Additional analyses

2.5.3

For a more detailed evaluation, additional statistical tests will include the analyses of potential moderators or confounding variables. Thus, we will check for possible pre-treatment differences between IG and CG in healthcare service utilization, demographic variables, and eating disorder symptom severity by conducting independent *t*-tests and chi-square tests. In case of significant group differences, these variables will be added as moderators of the treatment × time interaction effects to test the robustness of the findings. Further covariates possibly affecting the primary outcomes such as patient outcome expectancies, patient adherence, satisfaction, attitudes towards psychological online interventions, or emotion regulation will be included in our analyses.

Moreover, we will analyze the weekly assessments of eating disorder symptoms and the data from the EMA. This will allow us to examine changes in core eating disorder symptoms with a higher ecological validity and temporal resolution. As patient safety indicators, the percentage of participants in the IG who experienced adverse intervention effects caused by the intervention will be quantified, and the amount of impairment due to these adverse effects will be calculated. Further, changes in emotion regulation difficulties and strategy use in patients both on a habitual level and in daily life will be evaluated as potential moderators and mediators of symptom reduction in BN.

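### Demographics, symptom severity and healthcare use are tested as moderators only if the randomised arms happen to differ on them at baseline, a rule unrelated to effect modification

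*Protocol article*

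**What the plan says.** Section 1.1 (Background and rationale) states the aim: "Our second goal is to explore how web-based interventions can affect symptom changes and whether patient characteristics influence treatment outcomes". Section 3.2 (Conclusion) lists it among the trial's contributions: "our study will add knowledge on potential predictors of treatment outcomes and mechanisms of change".

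Section 2.5.3 (Additional analyses) opens by announcing analyses of possible moderators or confounders, and carries this out as follows:

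- The arms are compared by t-tests and chi-square tests, to "check for possible pre-treatment differences between IG and CG in healthcare service utilization, demographic variables, and eating disorder symptom severity".
- "In case of significant group differences, these variables will be added as moderators of the treatment × time interaction effects". The stated purpose is to check that the findings are robust.
- A second group is included with no such condition: "Further covariates possibly affecting the primary outcomes such as patient outcome expectancies, patient adherence, satisfaction, attitudes towards psychological online interventions, or emotion regulation".
- Changes in emotion regulation difficulties and strategy use, also without a condition, "will be evaluated as potential moderators and mediators of symptom reduction in BN".

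Section 2.5 (Statistical methods) lists moderator and mediator analyses as part of its fourth step, again without a condition.

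**The concern.** The rule in 2.5.3 treats two questions as one. Whether the arms differ on a variable at baseline bears on chance confounding of the comparison. Whether the variable changes the size of the treatment effect is a separate matter. A perfectly balanced characteristic can be a strong moderator, and an imbalanced one need not be a moderator at all.

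For demographics, severity and healthcare use, this rule is the only route to a moderator term that the article names. If it is followed as written, the usual result for any one of these variables is that no moderator estimate is produced. Where one is produced, chance imbalance chose the variable, not its clinical or theoretical relevance. A reader of the results could not tell an absence of effect modification from an absence of testing.

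**Working it through.** **Inputs.** From 2.3.1: 1:1 randomisation. From 2.5.1: three repeated assessments. From 2.6: d = 0.50, intraclass correlation .40, power .80, alpha .05, N = 152. The article does not give the level of the baseline tests, the number k of variables screened, or the sidedness of alpha. I assume .05 for the baseline tests, independence between them, k from 3 to 20, and two-sided alpha.

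**Step 1: reproduce the plan's sample size.** Take a random-intercept growth model with times 0, 1, 2, total variance 1, residual variance 1 − .40 = .60 and no random slope.
- Slope difference per interval: 0.50 / 2 = 0.25.
- Variance of one patient's slope: .60 / 2 = .30.
- n per arm = 2 × .30 × (1.960 + 0.842)² / 0.25² = 75.35, rounded up to 76.
- N = 152, as stated. Power at 76 per arm is .803.

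The planning figure is right, and the same model can be used for step 3.

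**Step 2: how often the condition is met.** Under randomisation every baseline difference is due to chance, so each variable passes with probability .05 and fails with probability .95. For k independent variables, P(none tested) = .95^k and the expected number tested = .05k.

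| k | P(none tested) | P(at least one tested) | Expected number tested |
|---|---|---|---|
| 3 | .86 | .14 | 0.15 |
| 5 | .77 | .23 | 0.25 |
| 10 | .60 | .40 | 0.50 |
| 15 | .46 | .54 | 0.75 |
| 20 | .36 | .64 | 1.00 |

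These figures apply only to the variables under the condition. They do not measure how often the second goal as a whole goes unanswered.

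**Step 3: what an unconditional test could show.** In units of d, the standard error of the treatment effect at 76 per arm is sqrt(4 × .60 / 76) = .178. For a characteristic that splits the sample into two equal halves (assumption), the standard error of the difference between the halves is twice that, .355. Two-sided power at .05:
- difference 0.50: 0.50 / .355 = 1.41, power .29
- difference 0.75: power .56
- difference 1.00: power .80

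Testing every listed characteristic raises its chance of being examined from about .05 to 1, but the estimates will be imprecise and must be labelled exploratory.

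**Step 4: what the unconditional items cover.**
- Expectancies, attitudes and emotion regulation are measured at study entrance (Table 2) and could serve as baseline characteristics. Section 2.5.3 does not say whether they enter as main effects or as interactions with treatment and time. A main effect describes prognosis over both arms, not who benefits.
- Adherence arises after randomisation and concerns use of a programme that controls cannot reach for 12 weeks (2.3.3, 2.4.7), so it cannot be a treatment × characteristic moderator. The same holds for satisfaction if satisfaction with the programme is meant.
- The emotion-regulation moderators named explicitly are changes during the trial. They suit mediation, but they are not characteristics at entry.

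**The case against.** The strongest reply is that the plan does contain unconditional analyses: step four in 2.5, the further covariates, and the emotion-regulation moderators and mediators. Section 1.1 names moderators, mediators and predictors as separate things, and a covariate's association with outcome is what a predictor analysis estimates. The conditional rule is offered as a robustness check, not as the analysis for the second goal. An itemised list of exploratory moderators is also something a condensed article may leave to the full plan or its analysis script.

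Much of this stands. A reader might infer that patient characteristics are tested as moderators only after imbalance, that the second goal has no analysis able to answer it, or that section 3.2 promises knowledge the plan cannot supply. The documents do not support those readings. The unconditional items partly cover the goal, and the covariate models can partly answer the wording about predictors. Nor does the article say that the further covariates enter as main effects only. The form is simply left open.

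What does not stand is the defence of the rule itself. Section 2.5.3 introduces the moderator analyses and then, as their consequence, turns to baseline tests. For demographics, severity and healthcare use it names no other moderator test. That is a stated selection rule which selects on the wrong criterion, so it is more than missing detail.

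**Conclusion.** The point holds for three groups of variables: demographics, eating disorder severity and healthcare use. Each has about a 95% chance of never being examined as a moderator, and any that is examined was selected by chance. With 5, 10 or 20 such variables, the chance that none is tested is about 77%, 60% or 36%. This rests on a .05 level and independence for the baseline tests, and on an assumed number of variables, none of which the article states.

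It does not extend to the second goal as a whole. No stated figure is wrong, and N = 152 reproduces. The analyses concerned are exploratory, and the primary comparison is untouched. The change is worth making because the rule serves a stated aim badly and the remedy is cheap.

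**What to change.** In 2.5.3, separate the moderator analysis from the baseline-imbalance check.

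1. Name a short list of pre-randomisation characteristics already collected. Examples are baseline symptom frequency, EDE-Q global score, demographics, baseline healthcare use, years since illness onset, and baseline PATHEV, APOI and DERS. For symptom frequency, the interview count already used for imputation in 2.5.2 avoids having the first outcome measurement also serve as the moderator.
2. Test each by a treatment × time × characteristic term in all randomised patients, whether or not the arms differ on it.
3. Say whether the further covariates enter as main effects or as interactions, and keep variables that arise after randomisation out of the baseline moderator list.
4. Report estimates with confidence intervals, labelled exploratory, and word section 3.2 to match.

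The cost is a few sentences and a few extra models on data already being collected. The article describes recruitment as ongoing, so the list can be fixed before outcomes are analysed. The downside is a larger number of exploratory tests with wide intervals.

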## Abbreviations

APAAmerican Psychiatric AssociationAPOIAttitudes Towards Online InterventionsAZAktenzeichen [file number]BMIBody Mass IndexBNbulimia nervosaBPtKBundespsychotherapeutenkammer [German national association of psychotherapists]CBTCognitive-Behavioral TherapyCGcontrol groupCIAClinical Impairment AssessmentCONSORTConsolidated Standards of Reporting TrialsCSSRIClient Sociodemographic Service Receipt InventoryDERSDifficulties in Emotion Regulation ScaleDSMDiagnostic and Statistical Manual of Mental DisordersDIPS-OADiagnostic Interview for Psychological Disorders-Open AccessEDEEating Disorder Examination InterviewEDE-QEating Disorder Examination QuestionnaireEMAecological momentary assessmentEUEuropean UnionGAD-7Generalized Anxiety Disorder ScaleHFERSTHeidelberg Form for Emotion Regulation StrategiesICCintraclass correlation coefficientIGintervention group*i*PCQProductivity Cost QuestionnaireLOCFlast observation carried forwardMICEmultiple imputations by chained equationsMLMmixed linear modeling*i*MTAInstitute for Medical Technology AssessmentNEQNegative Effects QuestionnairePATHEVPatients' Therapy Expectation and Evaluation ScalePHQPatient Health QuestionnairePICOPopulation Intervention Compared OutcomeRSESRosenberg Self-Esteem ScaleSPIRITStandard Protocol Items: Recommendations for Interventional TrialsWBQWeekly Binges QuestionnaireWHO-5World Health Organization-5 Well-Being Index

## Trial status

Recruitment started in January 2021 and is still ongoing. The first patient was enrolled in the study on January 25th, 2021. Assessments are expected to be completed by May 2022.

## Ethics approval and consent to participate

Ethics approval has been obtained from the institutional review board at Heidelberg University (AZ Tim 2020 1/1). Informed consent will be obtained from all participants, and the trial will be conducted in compliance with the Declaration of Helsinki and good clinical practice. International data privacy regulations and EU legislation will be considered.

## Availability of data and material

The de-identified and anonymized data and the R analysis script of the current trial will be made available on the *Open Science Framework* (https://osf.io/zdnea/?view_only=b204c63d3d6c4d569e5a140927708eb6).
